### Inclusion criteria

To be enrolled, participants must be phase I–III patients with initial treatment of radical distal gastrectomy and satisfying the following inclusion criteria:Histologically proven stage I–III gastric cancer, evaluated as radically resectableNo synchronous or metachronous cancersPatients have signed informed consent formsAge 18–75 years oldNo malfunction of cardio-pulmonary, liver, and kidney, ECOG score 0–1No emergency surgery needed

### Exclusion criteria

Patients will be excluded according to the following criteria:Pregnant or lactating womenDistant metastasis to the liver, lung, bone, supraclavicular lymph nodes, pelvic, or ovarian species and peritoneal disseminationAscites or cachexiaSuffering from other serious diseases, including cardiovascular, respiratory, kidney, or liver disease, poorly controlled hypertension or diabetesParticipation in other clinical trials 4 weeks before the enrollment of this trial or still participating in other trialsMental illnessSurgical history whose influence has not been eliminatedHistory of another gastric or esophageal malignancy, including stromal tumor, sarcoma, lymphoma, and carcinoidActive infection with a fever of over 38°CPoor complianceNot suitable for this trial because of other clinical or laboratory conditions determined by the researchers

### Elimination criteria

Efficacy evaluation of primary outcome: if data for more than three of a total of six time-points (6 months, 1 year, 2 year, 3 year, 4 year, and 5 year) missed for the patient.Did not evaluate the efficacy according to the predetermined plan.

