### Sample size

Our study is designed as a superiority trial whose primary outcome is postoperative reflux gastritis or not. Current experience suggests the predicted rate of postoperative reflux gastritis will be 8% for the uncut Roux-en-Y anastomosis group and 12% for the control group of Billroth II anastomosis. The difference test was used to estimate the sample size with 80% test power and a 5% significance level. Accounting for a 15% drop-out rate and the 1:1 allocation ratio, the total number of patients required per group is 416 (832 in total), which was calculated using the software PASS version 11.0. Considering a completion rate of 75% for each coordinating center, 1040 envelopes were designed for random allocation. The number of cases will be increased if necessary according to the results of the interim analysis.

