### Outcome measures

All patients enrolled in this trial will be followed up regularly at stated intervals after the surgery for an average of 5 years. During the follow-up visits, patients will undergo endoscopy, laboratory tests, and radiography if necessary as described in Table 1.

**Table 1 Tab1:** Summary of the follow-up visit schedule and assessed parameters at each time point

	Preoperative	3 M	6 M	9 M	12 M	18 M	24 M	36 M	48 M	60 M
Endoscopy	*	**	*		*		*	*	*	*
Laboratory	*	*	*		*		*	*	*	*
CT scan	*	*	*		*		*	*	*	*
Upper digestive tract radiography	**	*	*		*		*	*	*	*

*Evaluation at the designated time point, **evaluation if necessary

The primary assessment indices of the study are reflux gastritis, esophagitis, bile regurgitation, and anastomotic ulcer. Endoscopy will be used to help with standardized assessment of these indices during the follow-up visits. Full details for the Los Angeles classification of the severity of reflux esophagitis are shown in Table 2.

**Table 2 Tab2:** Los Angeles classification of the severity of reflux esophagitis

Grade	Manifestation
A	One (or more) mucosal break(s) no longer than 5 mm that does not extend between the tops of two mucosal folds
B	One (or more) mucosal break(s) more than 5 mm long that does not extend between the tops of two mucosal folds
C	One (or more) mucosal break(s) that is continuous between the tops of two or more mucosal folds but which involve(s) less than 75% of the circumference
D	One (or more) mucosal break(s) that involve(s) at least 75% of the esophageal circumference

The secondary assessment indices are nutritional status, quality of life, perioperative complications, overall survival rate, and others. Nutritional status includes body mass index (BMI), hemoglobin, albumin, total protein, pre-albumin, transferring, and other indices such as appetite and Onodera’s prognosis nutritional index (PNI). Quality of life will be assessed by the gastrointestinal symptom rating scale (GSRS) and Visick score (shown in Additional file 1: Tables S1 and S2). Perioperative complications occurring within 30 days after the surgery include anastomotic fistula and anastomotic stenosis. Overall survival rates for 1, 3, and 5 years after the surgery as well as recurrence and metastasis rates will be calculated. Other indices include surgery time, intraoperative blood loss, length of hospital stay, and hospital cost.

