Moreover, we plan to do some subgroup analysis using the different preoperative nutrition status or the postoperative pathological stages as analysis factors. In our trial, region supervisors will monitor the researchers with regard to completeness of data collection. However, it is unavoidable to have some missing data. As we mentioned in the “Elimination criteria” section, patients whose efficacy evaluation data for the treatment are incomplete will be excluded. Other missing data are divided into two kinds—important data and common data—depending on the relationship of the missing data and the primary or secondary assessment of the trial. We will record and report the number of cases where the randomized treatment cannot be performed. We will try to fix the common data using statistical tools. However, if the missing data are important, we will employ a specialist of statistics to analyze and decide how to deal with them.

However, bias exists in all clinical trials. In our trial, the blinding of the surgeons and patients as to the intervention is the most challenging aspect of designing a randomized controlled trial involving surgical procedures. For others, the blinding of patients should also be considered to reduce potential bias. Therefore, we set purely objective variables as the primary endpoints, including endoscopy and laboratory tests. Additionally, multicenter trials are associated with biases, including differences in operative skill. We have tried to eliminate these biases by examining the surgical procedure by another hospital and training all surgeons at participating centers in standard procedures.

To conclude, based on previous efforts in the reconstruction of distal gastrectomy, the proposed CSGC002 trial represents a multi-center, prospective, randomized controlled trial to test the hypothesis that uncut Roux-en-Y anastomosis can reduce postoperative complications and improve the nutritional status of gastric cancer patients after D2 gastrectomy compared to Billroth II anastomosis. We believe that the results of the trial will significantly contribute to the evidence on which to base the reconstruction of distal gastrectomy.

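### The elimination rule removes randomised patients who leave before the 2-year visit from the primary-outcome evaluation, even when reflux gastritis has already been recorded

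*Protocol article*

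**What the plan says.** The Elimination criteria section of the protocol article has two items. The first is headed "Efficacy evaluation of primary outcome" and removes a patient "if data for more than three of a total of six time-points" are missing, listed as "6 months, 1 year, 2 year, 3 year, 4 year, and 5 year) missed for the patient". The second removes patients under the words "Did not evaluate the efficacy according to the predetermined plan", without saying what counts. Neither item makes an exception for a patient whose outcome is already known.

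The Sample size section makes the outcome binary: the "primary outcome is postoperative reflux gastritis or not". Outcome measures says how it is seen: "Endoscopy will be used to help with standardized assessment of these indices during the follow-up visits". Table 1 there schedules endoscopy at 6, 12, 24, 36, 48 and 60 months, which are the six time-points of the elimination rule.

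The Discussion refers back to the Elimination criteria section but words the rule without a threshold: "patients whose efficacy evaluation data for the treatment are incomplete will be excluded". On other gaps it says: "if the missing data are important, we will employ a specialist of statistics to analyze and decide how to deal with them".

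**The concern.** The rule defines who is analysed by what happens after randomisation. A patient with reflux gastritis on the 6- or 12-month endoscopy who then dies or stops attending has a known primary event, and the rule deletes it. A patient with the same finding who keeps attending until 2 years is counted.

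Whether someone is still attending at 2 years can depend on symptoms, and so on the outcome. It can also depend on arm. Under Randomization the surgeon learns the arm during the operation, and the Discussion concedes that blinding is difficult in this setting. If the link between having reflux gastritis and leaving differs between arms, the two retained groups are no longer comparable and the observed difference shifts. The planned difference is only 4 percentage points, so a modest shift matters.

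**Working it through.** **Inputs.** Six time-points and removal at more than three missed (Elimination criteria). 416 per group, 832 in total; rates of 8% (uncut Roux-en-Y) and 12% (Billroth II); 15% drop-out (Sample size). The article gives no figure for how many patients the rule will remove, so there is none to reproduce. (The 416 itself does not follow from the stated rates and power: 882 per group two-sided or 695 one-sided, before drop-out. That is a separate matter on which nothing below depends.)

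**Step 1: who is removed.** Missed visits by last visit attended, with none skipped before it:

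| Last visit | Missed of 6 | Elimination criteria | Discussion, read literally |
|---|---|---|---|
| none | 6 | removed | removed |
| 6 months | 5 | removed | removed |
| 1 year | 4 | removed | removed |
| 2 years | 3 | kept | removed |
| 3 years | 2 | kept | removed |
| 4 years | 1 | kept | removed |
| 5 years | 0 | kept | kept |

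Leaving before the 2-year visit always leads to removal. Over all 2^6 = 64 attendance patterns, the Elimination criteria remove 15 + 6 + 1 = 22 (four, five or six missed). The literal Discussion wording removes 63. They differ on 63 − 22 = 41.

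**Step 2: how many patients.** Assume a total loss D over 5 years at a constant hazard. The share gone before 2 years is f = 1 − (1 − D)^(2/5).

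| D | f | Removed, Elimination criteria (832 × f) | Removed, Discussion read literally (832 × D) |
|---|---|---|---|
| 15% | 6.3% | 52 | 125 |
| 25% | 10.9% | 90 | 208 |
| 40% | 18.5% | 154 | 333 |

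Only the 15% comes from the protocol. The other rows show sensitivity.

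**Step 3: how many events.** Expected events are 416 × 0.08 + 416 × 0.12 = 33.3 + 49.9 = 83.2. If leavers carry average risk, 0.063 × 83.2 ≈ 5 belong to removed patients. If all of the 15% left before 2 years, it would be 0.15 × 83.2 ≈ 12. Both are ceilings for *recorded* events at that risk, because only events seen before the patient left can be discarded.

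**Step 4: bias with no true effect (illustrative).** Take a true rate of 12% in both arms, with a share e removed per arm. Assume a risk r of 25% among removed uncut Roux-en-Y patients and 12% among removed Billroth II patients. The retained rate is (0.12 − e × r)/(1 − e).

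- e = 0.063: (0.12 − 0.063 × 0.25)/0.937 = 11.1% against 12.0%, a spurious 0.9 points.
- e = 0.15: (0.12 − 0.15 × 0.25)/0.85 = 9.7% against 12.0%, a spurious 2.3 points.

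Swapping the arms reverses the sign.

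**Step 5: bias with the planned effect (illustrative).** Let 6% of non-cases leave before 2 years, and let q be the share of cases who do. The retained rate is p(1 − q)/[p(1 − q) + (1 − p) × 0.94].

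| q, uncut Roux-en-Y | q, Billroth II | Observed rates | Difference (points) |
|---|---|---|---|
| 6% | 6% | 8.0% v 12.0% | 4.0 |
| 6% | 20% | 8.0% v 10.4% | 2.4 |
| 6% | 30% | 8.0% v 9.2% | 1.2 |
| 30% | 6% | 6.1% v 12.0% | 5.9 |

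The rule is harmless if leaving is unrelated to the outcome. Otherwise it can shrink or inflate the effect.

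**The case against.** Five points can be made for the plan.

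- **Size.** A reader might infer that the whole 15% drop-out is eliminated, hence 125 patients, about 12 events and a 2.3-point bias. The Elimination criteria do not support that, because patients who leave after the 2-year visit are kept. Those figures need either all drop-out before 2 years or the Discussion taken literally. This objection stands.
- **Relapse.** A reader might infer that relapse triggers the rule. Nothing in the Elimination criteria or Outcome measures ends endoscopy at recurrence, so a relapsed patient may go on attending. The restriction on recurrence is a separate sentence at the end of Outcome measures. Nor does the rule say whether visits after death are missed. Both stand, and the second is an assumption here.
- **Two rules.** A reader might infer that the Discussion sets a second, stricter rule. It points back to the Elimination criteria and may be a loose paraphrase. What remains is a wording difference to reconcile.
- **Missing data.** A reader might infer that the method will be chosen with the results in view. The article defers to a statistician without saying when, or whether with knowledge of arm, and the analysis plan, which is not shown, may settle it. No finding is made on this.
- **Endpoint.** Discarding known events presupposes that an event at any visit settles the outcome. The article gives the binary outcome no time point, so this is the natural reading but not a stated one.

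None of this touches the core. The rule is stated in the Methods, applies to the primary outcome, and has no exception for a recorded event. It is not a detail left to the analysis plan: a plan that follows the article inherits it, and one that does not contradicts it.

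**Conclusion.** The concern holds. As written, the rule removes every patient whose last visit falls before 2 years, whatever was recorded earlier, provided that unattended visits (including those after death) count as missed. It is a post-randomisation exclusion that can depend on outcome and arm, and the direction of bias cannot be known in advance.

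The probable size is moderate: about 52 patients and at most about 5 expected events, assuming 15% loss at a constant hazard and average risk among leavers. At that 15% loss, 125 patients and about 12 events are the ceiling. The illustrative null bias of 0.9 to 2.3 points, against a planned 4, rests on an assumed 25% v 12% risk contrast. It shows what is possible and is not a forecast.

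**What to change.** - Do not apply the elimination rule in the primary analysis. Analyse all randomised patients in their assigned arm, and make the recurrence restriction at the end of Outcome measures consistent with that set.
- Count as an event any reflux gastritis documented at a scheduled endoscopy, and state the period over which the outcome is assessed. The article names no primary visit, so the method should not depend on one.
- Handle incomplete follow-up by one method fixed before unblinding: for example, cumulative incidence with death as a competing event, or multiple imputation of event status.
- Keep the present rule as a sensitivity analysis. For that purpose, say whether visits after death count as missed, and define the second elimination item.
- Bring the Discussion's wording into line with the Elimination criteria.

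The cost is protocol and analysis-plan wording and modest extra analysis. No new data are needed.

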### Recruitment

Patient recruitment from the centers began on 1 January 2016 and will be finished in December 2018 or when the required number of participants has been obtained, whichever is sooner. Eligible patients will be informed about the trial, allowed to ask questions about the study as well as treatments, and invited to participate in the trial.

### Randomization

After completing an initial assessment and signing an informed consent form, participants will be randomized into two groups: the experimental group undergoing uncut Roux-en-Y anastomosis and the control group undergoing Billroth II anastomosis.

The randomization is undertaken only by the qualified researchers. A secure randomization routine will give each patient an identification number. This number must be recorded in the randomized list together with the randomized data. The completed list should be signed by the investigators and submitted to the data center along with the patients’ initial information. Patients’ identification numbers should be marked in all the relevant reports.

During the randomization, allocation concealment should be maintained. All the patients will be randomized into groups in a 1:1 ratio, and neither surgeons nor patients will be informed as to the randomization arm before surgery. Once D2 gastrectomy has been performed, the randomization arm of the patient will be revealed and the corresponding anastomosis will be performed.

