### Uniformity in surgical performance

Assuring uniformity in surgical performance is the key point for our multi-center clinical trial. Therefore, the surgeons definitely should be trained and the operative procedures monitored. It is worth mentioning that the surgeons should at least have clinical experience in conducting radical gastrectomy for more than 3 years or more than 100 cases.

Before the trial, the leading center will appoint qualified surgeons to train the other surgeons in the coordinating centers. It is relatively easy for them to master the new technique for the reason that the uncut Roux-en-Y anastomosis is based on Billroth II anastomosis with the addition of the side-to-side anastomosis between the jejunum approximately 35 cm from gastrojejunostomy and the jejunum approximately 5 cm from the ligament of Treitz and closure of the intestinal cavity on the input less than 5 cm from the loop gastrojejunostomy anastomosis using uncut closure devices.

In particular, it is required to take pictures of the surgery field including the lymph node dissection area and the anastomosis field in order to make sure that the performance is qualified. These pictures will be uploaded to the database and checked by the data managers. If the operation does not achieve the standard of either D2 gastrectomy or corresponding anastomosis, the case will be rejected.

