#### Case report form

In the trial, observation or examination items need to be recorded in the CRF. The contents of the CRF should be identical to the original materials. In the CRF, the results calculated from the original materials should be able to be back-dated.

The CRF must be filled in with the following criteria satisfied:Use black pen or black ball-point pen to fill in data.Data from patients who have signed informed consent and met inclusion criteria, but who are subsequently judged to fail to meet inclusion criteria after treatment or even without drug treatment, should be recorded in the CRF.Draw on the original record with horizontal lines when making corrections (correction fluid is not allowed). Make sure the original record is identifiable and then sign and date the correction.For items not yet examined, “ND” should be marked in the CRF.

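### Patients are randomised after consent but the arm is used only once D2 gastrectomy is done, so patients who can receive neither anastomosis enter the randomised set

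*Protocol article*

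**What the plan says.** The Randomization section gives the order of events. First: "After completing an initial assessment and signing an informed consent form, participants will be randomized into two groups". Then "neither surgeons nor patients will be informed as to the randomization arm before surgery". Finally: "Once D2 gastrectomy has been performed, the randomization arm of the patient will be revealed and the corresponding anastomosis will be performed".

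Entry requires stage I–III disease evaluated as radically resectable, in patients whose initial treatment is radical distal gastrectomy (Inclusion criteria). Distant metastasis and peritoneal dissemination exclude (Exclusion criteria).

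Three other places deal with patients for whom this does not work out:
- Uniformity in surgical performance: "If the operation does not achieve the standard of either D2 gastrectomy or corresponding anastomosis, the case will be rejected".
- Case report form: data from consented patients "who are subsequently judged to fail to meet inclusion criteria after treatment or even without drug treatment, should be recorded in the CRF".
- Discussion: "We will record and report the number of cases where the randomized treatment cannot be performed".

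On allocation material, Sample size says: "Considering a completion rate of 75% for each coordinating center, 1040 envelopes were designed for random allocation".

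**The concern.** An arm that is withheld before surgery and revealed later has already been assigned, so the natural reading is that allocation precedes the operation. Some of what makes a patient suitable for the comparison may become clear only during the operation: whether there is peritoneal or other metastatic disease, and whether a radical distal gastrectomy is what is actually performed. A patient who fails on either count already belongs to the randomised set but has no reconstruction of either kind.

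The trial then has two unattractive options. Rejecting the patient is a post-randomisation exclusion and uses up sample size. Keeping the patient adds someone without the intervention under test and pulls the two arms together. The early assignment has no stated purpose, since nothing is done with the arm until D2 gastrectomy is complete.

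**Working it through.** **Order of events.** Set side by side, the sections give: initial assessment and consent, randomisation, operation, D2 gastrectomy performed, arm revealed, anastomosis. Eligibility is not re-checked between the start of the operation and the reveal as a condition of being randomised. The Discussion expects some cases in which the randomised treatment cannot be performed, but only counts them.

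**Inputs.** Sample size gives 8% against 12%, 80% power, 5% significance, 15% drop-out and 416 per group. Sidedness is not stated. The share *q* of randomised patients who never reach reconstruction is not given either; 5% and 10% are assumptions.

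**The plan's own figure.** Per-group size by the normal approximation with pooled variance under the null, where *p̄* is the mean of the two rates:

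n = [z_α √(2p̄(1−p̄)) + z_β √(p₁(1−p₁) + p₂(1−p₂))]² / (p₁−p₂)²

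- Two-sided: [1.960 × √0.18 + 0.842 × √0.1792]² / 0.04² = 882; 882/0.85 = 1,038 after drop-out.
- One-sided: 695; 695/0.85 = 818 after drop-out.

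Neither gives 416. That is a separate matter, but it explains why the baseline power below is low. Evaluable patients at the stated size: 416 × 0.85 ≈ 354 per group.

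**Power at the stated size.** Power = Φ{[(p₁−p₂)√n − z_α √(2p̄(1−p̄))] / √(p₁(1−p₁) + p₂(1−p₂))}. Two-sided with n = 354: Φ[(0.7526 − 0.8315)/0.4233] = 42.6%. One-sided: 55.1%.

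*If such patients are removed*, n becomes 416(1−q) × 0.85. *If they are kept*, and assuming they stay evaluable with no reflux gastritis in either arm, both rates are multiplied by (1−q) with n at 354.

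| q | of 832 | removed: power 2-sided / 1-sided | kept: difference | kept: power 2-sided / 1-sided |
|---|---|---|---|---|
| 0 | 0 | 42.6% / 55.1% | 4.0 points | 42.6% / 55.1% |
| 5% | about 42 | 40.8% / 53.3% | 3.8 points | 40.7% / 53.2% |
| 10% | about 83 | 39.0% / 51.5% | 3.6 points | 38.7% / 51.1% |

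The loss is about 2 points at 5% and about 4 points at 10%, whichever option is taken. To have 416 per group reach reconstruction, 416/0.95 = 438 per group (876 in total) or 416/0.90 = 463 per group (926) would have to be randomised.

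**Envelopes (separate from timing).** 1,040 × 0.75 = 780, which is 52 short of 832. At 75%, 832/0.75 = 1,109.3, so about 1,110 are needed. The stated 1,040 corresponds to 832/1,040 = 80%.

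**The case against.** The strongest reply is that concealment protects the comparison. A patient found to have dissemination, or to need another operation, is lost before anyone knows the arm, so the loss should be unrelated to arm. This stands: the cost is in numbers or dilution. A reader might infer that early randomisation biases the result, but the documents do not support that.

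Other stronger readings are tempting and also fail:
- A reader might take the Case report form section as permission to exclude patients found ineligible after treatment, when the arm is known. It is a rule on what to record and authorises no exclusion. The arm-aware removal is in Uniformity in surgical performance: cases are rejected after review of photographs that include the anastomosis field.
- A reader might take the 75% completion rate to mean that a quarter of patients fail at operation. That rate is given per centre to set envelope numbers and is not tied to operative findings.
- A reader might infer that concealment is endangered because investigators sign the randomised list. The section does not say when the list is completed or that it shows the arm, and it requires concealment.

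Three further points stand in part. Resectability is worded as an evaluation, which can be satisfied before surgery; that the operation may overturn it is an inference. The moment of the draw is not timed explicitly: if envelopes are in fact opened in theatre, the defect is one of wording, and the section should say so. Finally, the 15% drop-out allowance may already absorb some of this loss, though it is not linked to it.

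**Conclusion.** The point holds as a matter of efficiency and clarity. The Randomization section places randomisation ahead of the operation and the use of the arm after D2 gastrectomy, with nothing to keep patients who can receive neither anastomosis out of the randomised set. The cost is about 2 to 4 points of power at an assumed 5% to 10%, at the stated sample size; the true share is not in the document. The kept-and-diluted figures also assume that these patients remain evaluable and have no reflux gastritis.

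Losses before the reveal do not by themselves bias the comparison. The risk of bias lies in removals after it, namely rejection for a substandard anastomosis, and moving the draw alone would not remove that rule.

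The envelope mismatch is a minor arithmetic error in its own right and adds no weight to the timing point.

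**What to change.** In Randomization, change the sequence:
- Consent and register the patient before surgery.
- Open the envelope, and count the patient as randomised, only after the surgeon has confirmed in theatre that the entry criteria are met and D2 gastrectomy has been completed.
- Keep a log of patients consented but not randomised, with reasons.
- State that no entry or quality criterion removes a patient from the analysis after the reveal, and that all randomised patients are analysed as allocated. Amend the rejection rule in Uniformity in surgical performance to match: a substandard anastomosis may be recorded as a deviation, but the patient stays in.

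In Sample size, reconcile the envelope figure: either about 1,110 envelopes at 75% completion, or 1,040 at 80%.

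The cost is protocol wording and access to the allocation from theatre, at a point where the arm is already disclosed; no patients or procedures are added. Recruitment began in January 2016 and was due to finish by December 2018. A change made during enrolment would therefore create two differently defined randomised cohorts, and must be dated and reported. If enrolment has ended, the as-allocated rule can still be fixed before analysis.
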